#### Quantitative Analysis Plan

Analysis will begin by examining the psychometric properties, for example, internal consistency reliability using Cronbach alpha for all scales and subscales of established measures. Measures demonstrating insufficient reliability (eg, internal consistency <.70) in the study sample will be further examined with an exploratory factor analysis using Promax oblique rotation. Items with loadings <.40 or strong cross-loadings may be excluded for further analyses. Intercorrelations among items within each subscale and subscales within each measure will be examined; the correlation among measures will also be examined. Once reliability in the sample is established, descriptive analyses will be used to summarize the inner and outer contextual factors within and across sites and by informant (eg, site PIs and key implementers; clinical care providers and administrative staff). At baseline, we will examine mean differences in perceptions of intervention fit and attitudes toward EBP across site PIs and key implementers. We will also assess how perceptions vary as a function of Implementer demographics. At each follow-up, a comparison of changes in the inner and outer context factors over time (ie, from baseline to postintervention and sustainment) using a multivariate analysis will be conducted. Mixed linear effects models, adjusting for covariates, including age, time in position, role in clinic, experience level, and site-level factors, will be used to explore the impact these factors have on the overall implementation and sustainability of Scale It Up projects across sites and patient outcomes.

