**Results:**

The EPIS baseline period began in June 2017 and concluded in May 2018; analysis of the baseline data is underway. To date, 153 stakeholders have completed qualitative interviews, and 91.5% (140/153) completed the quantitative survey.

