### Participants and Targeted Sites

All medical providers and staff with patient contact (“Key Stakeholders”) at 13 ATN sites participating in the aforementioned Scale It Up research projects will be eligible to participate (Table 2). Patient contact is defined as having direct patient interaction across several points of care, including prevention, counseling and testing, linkage to care, HIV primary care, services to promote retention and adherence to medications, and other medical or psychosocial services. Key stakeholders will also include administrative and research staff with key decision-making roles (eg, division chief and clinic director) who will provide input on prevention and care services and site operations. Each site will identify a clinical leader (“Site PI”) to represent the organizational leadership perspective. There are no exclusion criteria. Participant turnover will be managed by maintaining the participant’s responses collected up to the point of separation as a part of the study data corpus, but participants will not be retained in the study post separation. Similarly, if a site discontinues its participation, participants associated with that site will remain part of the study data corpus. Newly hired medical providers and staff at the 2 follow-up points will be invited to participate. Different sites participated in different Scale It Up projects because of the differing nature of each EBP being tested and the hybrid design selected for each effectiveness-implementation trial (see the study by Naar et al [13] in this issue). For example, ATN 146 used providers as the participants, but the other 3 trials primarily used patients as the unit of analysis.

**Table 2 table2:** Scale It Up projects and participating sites in the Exploration, Preparation, Implementation, and Sustainment protocol.

Site	City, State	ATN^a^ 144 SMART^b^	ATN 145 YMHP^c^	ATN 146 TMI^d^	ATN 156 We Test
Johns Hopkins [name]	X^e^	—^f^	X	—
University of Alabama at Birmingham/Birmingham AIDS Outreach	Birmingham, AL	X	—	X	—
Center for HIV Educational Studies and Training at Hunter College^g^	New York, NY	—	—	—	X
State University of New York Downstate Medical Center	Brooklyn, NY	X	—	X	—
Wayne State University Prevention	Detroit, MI	—	X	—	X
Children’s Hospital of Los Angeles	Los Angeles, CA	X	—	X	—
St. Jude Children’s Research Hospital	Memphis, TN	X	—	X	—
University of Miami	Miami, FL	X	X	X	X
Tulane University^h^	New Orleans, LA	X	—	X	—

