Children’s Hospital of Philadelphia	Philadelphia, PA	X	X	X	—
University of California, San Diego	San Diego, CA	X	—	X	X
University of South Florida	Tampa, FL	X	—	X	—
Children’s National Health System	Washington, D.C.	X	—	X	—

^a^ATN: Adolescent Medicine Trials Network for HIV/AIDS Interventions.

^b^SMART: Sequential Multiple Assignment Randomized Trial.

^c^YMHP: Young Men’s Health Project.

^d^TMI: Tailored Motivational Interviewing Implementation Intervention.

^e^Site is participating in given SIU project and receives relevant questions for Exploration, Preparation, Implementation, and Sustainment model.

^f^Not applicable.

^g^Postimplementation and sustainment phase only.

^h^Preimplementation phase only.

Before each data collection effort, each site will provide a list of the medical providers and staff with direct patient contact. This list will include names, contact information (phone number and email), and role(s) within the clinic. Potential participants will receive an initial “enrollment email” introducing them to the EPIS model and study and providing them with instructions for scheduling their qualitative interview through a Web-based scheduling system. After the initial email, potential participants will be sent reminders every 2 weeks throughout the baseline study period about project enrollment. All sites have agreed to permit participants to participate in EPIS data collection efforts during their regularly scheduled work hours. Participants will be provided a list of available interview times from which they can choose an interview time most convenient for their schedule and availability. Participants will also be given the option of directly emailing their availability to arrange the most convenient interview. Interviewers are centralized, providing available times for all sites and will call participants at the scheduled time.

Upon completion of the interview, participants receive a link to complete the survey in Qualtrics. Participants who complete both the qualitative interview and quantitative survey receive a US $10 Amazon e-gift card. If a participant completes all 3 assessments (ie, preimplementation, implementation, and sustainment), they can receive a total of US $30 in Amazon e-gift cards. Participants who have not completed the quantitative survey will receive periodic reminders to do so for the duration of the data collection window.

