### Analysis Plan

The analyses will focus on understanding the barriers and facilitators located within sites’ inner and outer context that is associated with implementing and sustaining EBPs into HIV care settings. Analyses will be guided by the following questions: (1) How do inner context factors (eg, organizational culture and climate and leadership) influence EBP implementation and sustainment? (2) How do outer context factors (eg, fiscal viability and interorganizational networks) influence EBP implementation and sustainment? (3) To what extent do the perceptions of key stakeholders and clinical leaders (ie, site PIs) vary, and how does that variation affect EBP implementation and sustainment? (4) To what extent do stakeholder perceptions (key stakeholder and site PI combined) vary by site (ie, organizational structure)?

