#### Mixed-Methods Analysis Plan

To offer findings in ways that move beyond the particularistic view of EBP implementation within the sites, once all of the data are coded across all time points, we will adopt the innovation profile approach [34] originally developed for classroom research. The approach results in a multidimensional rubric to classify where an organization is in the process of developing its capacity to engage in a particular set of activities, in this case, the integration of EBPs into routine patient care. The dimensions and subdimensions of the matrix we develop, as well as descriptions of the behavioral indicators of exemplary, intermediate, emerging, and low capacity to integrate EBPs, will be derived from aggregating the data produced during the analysis to the site level. These data will be integrated with quantitative fidelity data collected by the intervention protocol teams with equal weight given to qualitative and quantitative data sources [35]. We will follow best practices for conducting mixed-method designs in the health sciences as outlined by the Office of Behavioral and Social Sciences Research [36]. These include employing rigorous procedures in the methods of data collection and analysis and integrating the multiple sources of data toward the goal of obtaining rich, descriptive output.

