## Results

EPIS data collection was launched in June 2017 and, at the writing of this paper, the first phase (Preparation) of data collection has concluded, and analyses are underway. A total of 140 of 282 eligible stakeholders completed both components of the first EPIS data collection. The baseline data collection window closed with a small proportion of providers (13, 8.5%) having partially completed the baseline assessment, that is, the qualitative component was completed, and the quantitative survey remains outstanding. About 20% (56) declined to participate and the remaining stakeholders did not respond to the enrollment invitation before the closure of the baseline data collection window. Figure 1 illustrates completion rates by site. Follow-up data collections are scheduled to begin in March 2019 (Implementation) and March 2020 (Sustainment).

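### Guiding question 4 is answered from the surveys only by descriptive site summaries, which at about 12 respondents per site mix true site differences with sampling noise

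*Protocol article*

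**What the plan says.** The Analysis Plan of the Protocol article lists four guiding questions. The fourth is "To what extent do stakeholder perceptions (key stakeholder and site PI combined) vary by site (ie, organizational structure".

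The Quantitative Analysis Plan then goes through the survey analysis in steps. After the reliability checks it states that "descriptive analyses will be used to summarize the inner and outer contextual factors within and across sites and by informant". Other contrasts get their own step: site leaders against implementers at baseline, respondent demographics, and change over time. The linear mixed models are reserved for the effect of the contextual factors on implementation, sustainability and patient outcomes. No survey step other than the descriptive summary addresses how far perceptions differ between sites.

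On numbers, the Results section reports that "A total of 140 of 282 eligible stakeholders completed both components of the first EPIS data collection". Eligible staff work "at 13 ATN sites participating in the aforementioned Scale It Up research projects will be eligible to participate". In the footnotes to Table 2, one site is marked "Postimplementation and sustainment phase only" and another "Preimplementation phase only". So 12 sites contribute at baseline and 11 at all three phases.

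The Mixed-Methods Analysis Plan adds a site rubric with four levels, whose source it gives as follows: "exemplary, intermediate, emerging, and low capacity to integrate EBPs, will be derived from aggregating the data produced during the analysis to the site level".

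**The concern.** A question about extent asks for a quantity: how much of the spread in perceptions lies between sites. The spread of raw site means does not estimate that quantity. It estimates the between-site variance plus the within-site variance divided by the number of respondents. With about a dozen respondents per site, the second term can be as large as the first or larger.

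If raw site summaries are read as the answer, ordinary differences between individual respondents will be reported as organizational variation. The sites that appear highest and lowest will be partly a product of chance, most of all sites with few respondents. If survey scales also enter the site profiles, the same noise goes with them.

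**Working it through.** **Inputs from the Protocol article**
- Abstract, Results: "153 stakeholders have completed qualitative interviews, and 91.5% (140/153) completed the quantitative survey". Check: 140/153 = 91.5%, and 13/153 = 8.5% partial completers. Both agree with the article.
- Results: 282 eligible, so 140/282 = 49.6% completed both components. 56 declined, and 282 − 153 − 56 = 73 did not respond.
- Sites: 13, less one absent at baseline = 12.
- Surveys per site: 140/12 = 11.67 on average (140/13 = 10.8 if all sites were counted). Actual counts are in Figure 1, which is not shown.

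**Assumptions.** The article gives no SD or ICC. I set the SD to 1, treat respondents as independent within site, take near-equal site sizes, and try ICCs of 0, 0.05, 0.10 and 0.20.

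**1. Gap between extreme site means when sites do not differ (ICC = 0)**
- Standard error of a site mean: 1/√11.67 = 0.293 SD.
- Expected range of 12 independent standard normal values: about 3.26.
- Expected gap: 3.26 × 0.293 = 0.95 SD.
- A simulation of 100,000 studies (eight sites of 12, four of 11) agrees: mean 0.95, 5th to 95th percentile 0.60 to 1.36, and at least 0.8 SD in 74% of runs.

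**2. Variants, still with no true site differences**

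| Setting | Mean gap (SD) | Gap ≥ 0.8 SD |
|---|---|---|
| 12 sites, near-equal sizes | 0.95 | 74% |
| Unequal sizes, assumed 4 to 22 | 1.11 | 85% |
| Finite population, factor √(1 − 140/282) = 0.71 | 0.68 | 22% |
| Three waves of 12 pooled, 11 sites, within-person correlation 0.5 | 0.75 | 36% |
| Three waves of 12 pooled, 11 sites, independent waves | 0.53 | 3% |

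**3. How much of the variance of raw site means is real**

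Reliability = n·ICC / (1 + (n − 1)·ICC), with n = 11.67.
- ICC 0.05: 0.583/1.533 = 0.38
- ICC 0.10: 1.167/2.067 = 0.56
- ICC 0.20: 2.333/3.133 = 0.74

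The inverse is the factor by which the variance of raw site means exceeds the true between-site variance: 1/0.38 = 2.6, 1/0.56 = 1.8 and 1/0.74 = 1.3.

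**4. Can the raw spread tell these cases apart?**

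The simulated mean gap is 0.95 SD at ICC 0, 1.18 at 0.05, 1.37 at 0.10 and 1.69 at 0.20. The 5th to 95th percentile bands overlap heavily: 0.60 to 1.36 at ICC 0 against 0.87 to 1.94 at ICC 0.10. A reader shown only site means could not say which case applies.

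**5. What a variance-component view adds**

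A one-way F test on 12 sites and 140 respondents rejects in about 5% of studies when sites do not differ (5.3% simulated). At ICCs of 0.05, 0.10 and 0.20 its power is about 32%, 63% and 92%. So the data carry usable but limited information on site variation.

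**The case against.** The study calls itself descriptive, and an article need not list every interval or variance component; a fuller plan may supply them. Summarizing within as well as across sites suggests that within-site spread will be shown. Interviews, coded by site, also bear on question 4. This stands in part. It rules out saying that the plan cannot return a finding of no site difference, since a descriptive summary may carry SDs or intervals. It does not remove the point, because the article does assign a survey method to question 4, and an ICC is itself a descriptive quantity suited to a question about extent.

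The size can also be disputed. All eligible staff are invited, so if the target is the perceptions of these particular staff, the finite-population figure of 0.68 SD is the fairer one. That is a legitimate reading, but it treats the 140 completers as a random half of 282, whereas 56 declined, 73 did not respond and 13 left the survey undone. Pooling waves lowers the noise further without removing it.

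A reader might infer something stronger: that the rubric will name top and bottom sites by chance alone. The documents do not support this. The Mixed-Methods Analysis Plan states no ranking, quantile split or cut-off. It builds on coded data from all time points, integrates fidelity data, and does not name survey means as an input. Even for a rule based purely on survey means, with identical sites at the scale midpoint, the chance of at least one site in each extreme level runs from 86% with outer cut-offs at ±0.25 SD to under 0.1% at ±1 SD. The outcome depends on cut-offs that the article does not give.

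**Conclusion.** The point holds for question 4 and the survey scales. As stated, the method does not separate site variation from sampling noise. At the baseline sample size that noise alone spreads the extreme site means by about 0.95 SD, or about 0.68 SD under the finite-population reading. At ICCs of 0.05 to 0.20, between 62% and 26% of the variance of raw site means would be noise (1 − 0.38 and 1 − 0.74).

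These figures rest on the baseline average of 11.7 surveys per site, near-equal site sizes and assumed ICCs. Unequal sizes would widen the chance gap. The point does not extend to the rubric, except that any survey scale used there would bring the same noise with it.

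**What to change.** For each scale completed by several people per site, fit a linear mixed model with a random intercept for site. Report the between-site variance and the ICC with a confidence interval as the survey answer to question 4. Present shrunken (empirical Bayes) site means with intervals, beside or in place of the raw means. The spread of the shrunken means should not itself be read as the extent of site variation, because shrinkage makes it too narrow; the variance component serves that purpose. If survey scales are used in the site rubric, carry these estimates in with their intervals.

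The Implementation Citizenship Behavior Scale is completed only by the site leader. With one rating per site it cannot be decomposed this way and should be reported as a single rating.

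The cost is a few lines of analysis on data already collected, with a model family the plan already uses. Site contrasts will look smaller, and with 12 sites the ICC interval will be wide. For that reason a scale should not be discarded because its site variance cannot be distinguished from zero: with power of about 32% at ICC 0.05 and 63% at 0.10, real differences would often be lost.

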#### Mixed-Methods Analysis Plan

To offer findings in ways that move beyond the particularistic view of EBP implementation within the sites, once all of the data are coded across all time points, we will adopt the innovation profile approach [34] originally developed for classroom research. The approach results in a multidimensional rubric to classify where an organization is in the process of developing its capacity to engage in a particular set of activities, in this case, the integration of EBPs into routine patient care. The dimensions and subdimensions of the matrix we develop, as well as descriptions of the behavioral indicators of exemplary, intermediate, emerging, and low capacity to integrate EBPs, will be derived from aggregating the data produced during the analysis to the site level. These data will be integrated with quantitative fidelity data collected by the intervention protocol teams with equal weight given to qualitative and quantitative data sources [35]. We will follow best practices for conducting mixed-method designs in the health sciences as outlined by the Office of Behavioral and Social Sciences Research [36]. These include employing rigorous procedures in the methods of data collection and analysis and integrating the multiple sources of data toward the goal of obtaining rich, descriptive output.

## Results

EPIS data collection was launched in June 2017 and, at the writing of this paper, the first phase (Preparation) of data collection has concluded, and analyses are underway. A total of 140 of 282 eligible stakeholders completed both components of the first EPIS data collection. The baseline data collection window closed with a small proportion of providers (13, 8.5%) having partially completed the baseline assessment, that is, the qualitative component was completed, and the quantitative survey remains outstanding. About 20% (56) declined to participate and the remaining stakeholders did not respond to the enrollment invitation before the closure of the baseline data collection window. Figure 1 illustrates completion rates by site. Follow-up data collections are scheduled to begin in March 2019 (Implementation) and March 2020 (Sustainment).

**Figure 1 figure1:**
[figure not shown]
Total participant enrollment status per site till May 2018.

## Discussion

### Protocol Goal

Although EBPs have demonstrated success in the academic setting, many challenges can prevent an EBP’s successful implementation and sustainment in real-world clinical contexts. The goal of the EPIS IS study is to generate knowledge about the barriers and facilitators to the implementation and sustainment of EBPs into adolescent HIV prevention and clinical care settings. Understanding the factors that impact organizations, clinics, and practitioners throughout the EBP implementation process will facilitate the adoption of EBPs by tailoring implementation to fit within the needs and culture of the organization and/or clinic.

### Limitations

The EPIS sample is limited to the 13 participating ATN clinics and the medical providers and staff with direct patient contact within these clinical settings. These participants may not be representative of service providers in other contexts. This study and the Scale It Up program are focused on the implementation of EBPs in multidisciplinary adolescent HIV settings. The EPIS model was developed in child welfare [6,37] and has begun to be applied to other service sectors including behavioral health care [38] and juvenile justice [10]. In general, the findings from this research will add to the growing literature on IS and particularly the EPIS model, which will facilitate translation to other clinical settings.

### Implications

This study is the first IS study of EBP implementation in adolescent HIV settings. The knowledge gained from the EPIS study will strengthen the implementation and sustainment of EBPs in both adolescent prevention and clinical care contexts by offering insights into the barriers and facilitators of successful EBP implementation and sustainment in real-world clinical contexts.

## Abbreviations

ATN: Adolescent Medicine Trials Network for HIV/AIDS Interventions
DLS: Director Leadership Scale
EBP: evidence-based practice
EBPAS: Evidence-Based Practice Attitude Scale
EBPAS-50: Evidence-Based Practice Attitude Scale-50
EPIS: Exploration, Preparation, Implementation, and Sustainment Model
ICBS: Implementation Citizenship Behavior Scale
ICS: Implementation Climate Scale
ILS: Implementation Leadership Scale
IS: implementation science
MI: motivational interviewing
OCM: Organizational Climate Measure
PI: principal investigator
POS: Perceived Organizational Support Scale
